
#### Adverse Events

2.7.3

Adverse events will be defined as any untoward medical occurrence in a clinical trial participant that does not necessarily have a causal relationship with the treatment. Adverse events will be ascertained by surveying participants at 24 weeks. Based on this information, the Chief Investigator will determine causality in consultation with other investigators as needed. If the event is related to the trial in the opinion of the Chief Investigator (in consultation with other investigators as required), it will be deemed a related adverse event. A serious adverse event will be defined as any untoward medical occurrence that: (1) results in death; (2) is life‐threatening; (3) requires hospitalisation or prolongation of existing inpatient hospitalisation; (4) results in persistent or significant disability or incapacity; (5) is a congenital anomaly or birth defect; and/or (6) any other important medical condition which, although not included in the above, may require medical or surgical intervention to prevent one of the outcomes listed.

*Process measures:* A range of process measures will also be collected. Table 2 lists all process measures and their assessment timepoints.

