### Interventions

2.4

No e‐learning group: verbal OA information and strengthening exercise (control intervention)

Participants in this group will receive two consultations with a physiotherapist over Zoom videoconferencing software (Zoom Video Communications Inc., USA) over 6 weeks. Participants will be seen by the same physiotherapist for both consults (one of eight registered musculoskeletal physiotherapists from across Australia). The first of two physiotherapy consultations will be in approximately week 1 and the second in week 6 (none will be made beyond the end of week 7). The purpose of the consultations will be for the physiotherapist to provide verbal OA information and to prescribe a home‐based strengthening exercise programme. Physiotherapists will consult from their clinic and participants will be based at home or wherever is suitable (e.g., work). Electronic (REDCap) semi‐structured consultation notes will be recorded by the physiotherapist for each consultation. These will be reviewed by the research staff to ensure physiotherapist adherence to trial protocols. Participants will be provided an information booklet for reference about how to prepare for the first consultation and a booklet of strength exercises, as well as 4 coloured resistance exercise bands (red, green, blue, and black) for performing strengthening exercises at home, which they can keep beyond the trial. Those allocated to this group will be provided access to the e‐learning course on completion of their involvement in the study (completed 24‐week outcome measures).

*OA information/education component:* In consultation 1, the physiotherapist will provide verbal information about OA and its recommended management and address any related participant questions. The information will be scripted (script written by the research team in collaboration with the study's eight musculoskeletal physiotherapists) and aims to reflect what may be provided in a real‐world consult. In consult 2, the physiotherapist will allow up to 10 min to address any questions the participant may have about OA and its management. The physiotherapist will answer participant questions based on their clinical knowledge.

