### Outcomes

2.7

Baseline descriptive data and outcome measures are presented in Table 2. Baseline and 24‐week assessments will be completed remotely via online questionnaires (REDCap). Participants completing 24‐week assessments will be given a $AUD50 gift voucher in gratitude for their participation.

**TABLE 2 msc70156-tbl-0002:** Schedule of enrolment, intervention, and assessments.

[figure not shown] [figure not shown] [figure not shown]

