#### Monitoring

2.8.3

The research team will meet fortnightly to review recruitment and monitor trial progress.

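### The only stated source of adverse events is a participant survey at 24 weeks, yet serious events are defined to include death, which that survey cannot report

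*Protocol article*

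**What the plan says.** Section 2.7.3 (Adverse Events) fixes both method and time: "Adverse events will be ascertained by surveying participants at 24 weeks". Causality is tied to that source: "Based on this information, the Chief Investigator will determine causality in consultation with other investigators as needed". The same section then gives the seriousness criteria, beginning: "A serious adverse event will be defined as any untoward medical occurrence that: (1) results in death; (2) is life‐threatening". Later criteria include hospitalisation and lasting or significant disability.

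The other contacts that the article describes are not named as sources of adverse events:

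- **Assessments (section 2.7).** Baseline and 24-week assessments are remote online questionnaires.
- **Consultations (section 2.4).** There are two, at about week 1 and week 6, with none after the end of week 7. Semi-structured "consultation notes will be recorded by the physiotherapist for each consultation", and the stated reason for reviewing them is fidelity: "These will be reviewed by the research staff to ensure physiotherapist adherence to trial protocols".
- **Monitoring (section 2.8.3).** "The research team will meet fortnightly to review recruitment and monitor trial progress". Adverse events are not mentioned.

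The sample size (section 2.8.1) allows for 15% loss to follow-up.

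**The concern.** The ascertainment rule does not match the definition it serves. A dead participant cannot complete a questionnaire, so the first seriousness criterion cannot be met through the only stated route. More generally, anyone who does not answer at 24 weeks contributes nothing on harms, and causality is judged from the survey information alone.

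After the second consultation the article describes no scheduled contact until the 24-week questionnaire, although participants are asked to continue and progress the exercises on their own throughout. Followed as written, the plan could report no serious events when some had occurred among those not surveyed. At stake is the completeness of the safety statement, not the efficacy result.

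**Working it through.** **Inputs from the article.** 136 participants, 68 per arm, 1:1 allocation; 15% loss to follow-up; one adverse event survey at 24 weeks.

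**Reproducing the plan's figure.** The 15% is the input that matters here, so I checked that it is what produces 136. I took alpha 0.025 as two-sided (the article does not say) and adjusted for baseline with correlation 0.35.

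- Adjusted SD = 11 × √(1 − 0.35²) = 10.30.
- n per arm = 2 × [10.30 × (2.241 + 0.842) / 6]² = 56.07, rounded up to 57.
- Allowing for loss: 57 / 0.85 = 67.06, rounded up to 68 per arm, 136 in total. This matches exactly.

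**Participants outside the stated method.** 0.15 × 136 = 20.4, or 10.2 per arm. About 116 (58 per arm) would supply adverse event data. At other losses: 6.8 participants at 5%, 13.6 at 10% and 27.2 at 20%.

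**What could be missed.** The article gives no serious event rate, so the rates below are assumptions. They are taken as equal in those lost and those retained. Expected number missed = 20.4 × p; chance of missing at least one = 1 − (1 − p)^20.

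| Assumed proportion with a serious event by 24 weeks | Expected number missed | Chance of missing at least one |
|---|---|---|
| 1% | 0.20 | 18% |
| 2% | 0.41 | 33% |
| 5% | 1.02 | 64% |

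**If those lost have more events.** Let their rate be k times that of responders. The share of participants with events who are surveyed is 0.85 / (0.85 + 0.15k):

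- k = 1: 0.85 / 1.00 = 85%
- k = 2: 0.85 / 1.15 = 74%
- k = 3: 0.85 / 1.30 = 65%

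The multiplier k has no source in the article. At k = 1 the result is simply the response rate. These figures show sensitivity and are not estimates.

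**Why the denominator matters.** With no events reported in an arm, the one-sided 95% upper bound on the rate is 1 − 0.05^(1/n): 4.3% if all 68 are treated as observed, 5.0% if only the 58 surveyed are. Even the second figure assumes that those lost resemble those surveyed.

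**Death.** No arithmetic is needed. Whatever the rate, a death before 24 weeks cannot be self-reported.

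**The case against.** The strongest reply is that this is a journal article condensing a full protocol that is not shown. Spontaneous reports, withdrawals and expedited reporting are often left to that document, and Table 2, which holds the assessment schedule and process measures, is not legible here. That stands as a limit: the survey is the only stated route, not demonstrably the only one. It does not remove the point, because the article does more than stay silent. It names source, method and time, and bases causality on that source.

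Several stronger readings are tempting, and the article does not support them:

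- **People who stop exercising because of harm are not surveyed.** Stopping exercise is not loss to follow-up. The questionnaire is online, its completion earns a voucher, and nothing makes it conditional on continuing the programme.
- **Disability and hospitalisation cannot be detected.** Many people so affected can complete an online form at 24 weeks. Only death, or incapacity severe enough to prevent a response, lies beyond self-report.
- **Causality is judged with knowledge of the arm.** Section 2.3 does not say whether the Chief Investigator is masked.
- **The comparison of harms between arms is biased.** Both arms get the same consultations, the same strengthening programme and the same survey timing, and nothing shows that loss would differ by arm.

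It is also fair to say that a question at consultation 2 covers only about the first six or seven weeks, and that physiotherapists who know the allocation would ask it. Both limits are reflected in the fix.

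**Conclusion.** The point holds as a gap in safety ascertainment that should be closed. The stated method cannot deliver the first item of the stated serious event definition. It also leaves about 20 of 136 participants (about 10 per arm) without adverse event data at the planned 15% loss. A finding of few or no serious events could therefore be an under-count.

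How large an under-count rests on assumptions: the 15% is a planning allowance, and event rates and any excess among those lost are not given. A reader might infer that these events can never reach the trial team. The article supports only the narrower statement that the described method does not collect them; an event could still become known informally or through a procedure in the full protocol. The primary outcomes, the sample size and the main analysis are untouched.

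**What to change.** Change the ascertainment sentence in section 2.7.3 so that the 24-week survey stays and, in both arms, any event, hospitalisation or death learned of at a consultation, at withdrawal or during follow-up of 24-week non-responders is also recorded as an adverse event. One identically worded field in the existing REDCap consultation notes would serve the consultations.

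Report events among all randomised participants, give the number surveyed beside it, and show events by source. Keep the uniform 24-week survey as the basis for comparing arms, because the consultation question would be asked by unblinded physiotherapists. Where feasible, judge relatedness from a listing without allocation, and state whether this was done. If the full protocol already provides these routes, bring the article's sentence into line with it.

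Cost: one form field, one line in the withdrawal and non-response procedure, about a minute of consultation time, and possibly a minor ethics notification. Recording work rises slightly, and more minor events will be recorded. Treatment, assessment times, sample size and primary analysis do not change.

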### Data Analysis, Monitoring and Auditing

2.8

#### Sample Size Calculation

2.8.1

A total sample size of 136 (68 per arm) is required to detect a minimally clinically important difference in the physical function outcome of 6 WOMAC units (Angst et al. 2001) at 24 weeks between the two treatment arms with 80% power and an alpha of 0.025 (alpha of 0.05 split between the two primary outcomes), assuming a correlation of 0.35 between baseline and 24 weeks follow‐up, a standard deviation (SD) of 11 WOMAC units and 15% loss to follow‐up (Bennell et al. 2017; Hinman et al. 2024). This sample size is more than sufficient to detect a minimally clinically important difference of 1.8 NRS units in the NRS pain scale (Bellamy et al. 1992), providing > 98% power when assuming 15% loss to follow‐up, a SD of 2.3 NRS units and a correlation of 0.35 between baseline and 24 weeks follow‐up (Bennell et al. 2017; Hinman et al. 2024).

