Physiotherapists, as the primary providers of exercise treatment for knee OA, face various challenges in delivering detailed and accurate consumer education to address OA misconceptions to support exercise prescription. These include limited time, lack of confidence and insufficient expertise (Briggs et al. 2019). Indeed, people with OA have expressed their dissatisfaction with the quality and amount of OA information currently available to them (Wluka et al. 2016). Additionally, many people with OA encounter obstacles in accessing physiotherapy for ongoing care, such as high costs and limited availability (Dobson et al. 2016). Therefore, it is warranted to explore new, scalable and efficient methods for delivering consistent consumer education that supports exercise prescription, especially with minimal clinician contact, to potentially improve exercise outcomes.

To improve consumer access to high‐quality education information about OA and its recommended management, we developed a consumer‐focused e‐learning course informed by educational theory and evidence‐based OA recommendations (Nelligan et al. 2023). The course is freely available worldwide via the online education platform FutureLearn (see https://go.unimelb.edu.au/6ume). In a randomised controlled trial of 120 people, the course was found to improve OA knowledge in people with hip and/or knee OA when compared to a typical OA education intervention: an electronic OA information pamphlet available from a reputable consumer organisation (Nelligan et al. 2025). Building on this work, we now seek to explore whether the course can enhance clinical outcomes from home‐based exercise that is prescribed by physiotherapists in a limited number of consultations.

Specifically, our primary objective is to investigate whether the addition of the e‐learning course to verbal information on OA and its management and a home‐based strengthening exercise programme prescribed over two consultations with a physiotherapist enhances pain and/or physical function outcomes at 24 weeks in people with knee OA. We also aimed to explore whether the programme will improve secondary outcomes at 24 weeks and to identify the proportion of participants achieving minimum clinically important differences in the primary outcomes (experimental group compared to control group).

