## Methods

2

Two arm, parallel group, superiority randomised controlled trial (RCT) conducted at the University of Melbourne (trial sponsor). Reporting of this protocol complies with SPIRIT guidelines (Chan et al. 2015) and TIDieR (Hoffmann et al. 2014). Reporting of the trials findings will comply with CONSORT (Moher et al. 2012). The trial has been prospectively registered with the Australian New Zealand Clinical Trials Registry (ID: ACTRN12624000418572, 5th April 2024).

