#### Data Analysis

2.8.2

The analysis will include all participants according to their randomised allocation (intention‐to‐treat). Multiple imputation will be used as the primary analysis to account for missing data if more than 5% of one or both primary outcomes are missing at 24 weeks. For each primary and continuous secondary outcome, mean between‐group differences at 24 weeks will be estimated from multiple linear regression models. The proportion of participants in each group that show an improvement that reaches or exceeds the minimum clinically important difference in NRS pain (≥ 1.8 units) and WOMAC function (≥ 6 units) will be calculated. For this and each binary outcome, groups will be compared using risk ratios and risk differences estimated from logistic regression models. For the ordinal outcome, weight loss efforts, a proportional odds model will be fitted. All models will include adjustment for baseline values, where relevant, and the stratifying variable of the physiotherapist.

To assess whether the treatment effect differs for different subgroups, exploratory analyses will be undertaken to add interaction terms between the treatment arm and each potential moderator in the models for the primary outcomes. For these analyses, pre‐specified moderators will include baseline levels of OA knowledge (OAKS) (Darlow et al. 2022), pain self‐efficacy (ASES pain) (Lorig et al. 1989), fear of movement (Brief Fear of Movement Scale for Osteoarthritis) (Shelby et al. 2012), and perceptions of OA (illness perceptions) (B‐IPQ) (Broadbent et al. 2006).

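### The fixed 0.025/0.025 split between the two primary outcomes is valid, but Holm at the same familywise 0.05 would raise power for function, and for claiming both outcomes, by about 7 points at no extra sample size (optional improvement)

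*Protocol article*

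**What the plan says.** The Methods section describes a "Two arm, parallel group, superiority randomised controlled trial (RCT") with two primary outcomes at 24 weeks: walking pain (NRS) and WOMAC function. The Background section asks whether adding the e-learning course "enhances pain and/or physical function outcomes at 24 weeks in people with knee OA", so a claim on either outcome, or on both, is of interest.

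The Sample Size Calculation section gives the total as follows: "A total sample size of 136 (68 per arm) is required". For function, the target is a "minimally clinically important difference in the physical function outcome of 6 WOMAC units". The power and error settings are "80% power and an alpha of 0.025 (alpha of 0.05 split between the two primary outcomes". The remaining inputs for function are a baseline to follow-up correlation of 0.35, an SD of 11 and a 15% loss. For pain it takes a difference of 1.8 NRS units, an SD of 2.3, and the same correlation and loss, and gives power above 98%.

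The Data Analysis section says that the mean differences "will be estimated from multiple linear regression models" with adjustment for baseline values. The Randomisation and Blinding section leaves the detail to a separate statistical analysis plan, to be written while the biostatisticians are blinded to allocation. That plan is not at hand.

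**The concern.** Under a fixed split, function is always judged at 0.025, however clear the pain result is. If pain came in at p < 0.001 and function at p = 0.03, the trial could not claim function. A stepwise rule with the same familywise error could.

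This matters because the two outcomes are unevenly powered. Function drives the sample size and has about 80% power. Pain has more than 98%, so under the planned effects the pain hypothesis is nearly always rejected, and its 0.025 could then pass to function. The stake is the chance of claiming the second outcome, and so of claiming both.

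**Working it through.** **Inputs.** From the Sample Size Calculation section: differences 6 (function) and 1.8 (pain); SDs 11 and 2.3; baseline to follow-up correlation 0.35; 15% loss; 68 per arm; 0.025 per outcome. Two inputs are not given and are assumed:
- Tests are two-sided. Only this reproduces 136; one-sided 0.025 gives 56 per arm, total 112.
- The correlation between the two test statistics is varied from 0 to 0.9.

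**Step 1: reproduce the plan.** Baseline adjustment multiplies each SD by √(1 − 0.35²) = 0.9367, giving 10.304 for function and 2.155 for pain.

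n per arm = 2 × 10.304² × (2.241 + 0.842)² / 6² = 56.1, rounded up to 57. Then 57 / 0.85 = 67.1, rounded up to 68 per arm, total 136, as stated. The t-based count is 58, and 58 / 0.85 = 68.2.

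Pain: evaluable per arm = 68 × 0.85 = 57.8. Standard error = 2.155 × √(2/57.8) = 0.401. Standardised effect = 1.8 / 0.401 = 4.49. Power at 0.025 = Φ(4.49 − 2.241) = 98.8% (98.6% by the t distribution), consistent with the stated figure.

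**Step 2: function under each rule.** Standard error = 10.304 × √(2/57.8) = 1.917. Standardised effect = 6 / 1.917 = 3.130.
- At 0.025: Φ(3.130 − 2.241) = 81.3%.
- At 0.05: Φ(3.130 − 1.960) = 87.9%.

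Holm adds the cases in which function falls between the two thresholds and pain is rejected at 0.025. With uncorrelated outcomes the gain is (0.879 − 0.813) × 0.988 = 0.065, so power is 87.8%.

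**Step 3: both planned effects true, by correlation** (bivariate-normal simulation at 57.8 per arm):

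| Correlation | Function: split → Holm | Both: split → Holm | At least one: either rule |
|---|---|---|---|
| 0 | 81% → 88% | 80% → 87% | 99.8% |
| 0.5 | 81% → 88% | 81% → 88% | 99.2% |
| 0.9 | 81% → 88% | 81% → 88% | 98.8% |

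The last column is the same for both rules because Holm's first step, smaller p-value against 0.025, is also the fixed split's condition for at least one success. Power for pain moves only from 98.8% to between 98.8% and 99.3%.

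**Step 4: if the pain effect is smaller.** The same product, uncorrelated outcomes:
- Pain effect 1.0 NRS: Φ(1.0/0.401 − 2.241) = 0.60, so the gain is 0.066 × 0.60 = 4.0 points. Simulation at higher correlations gives less, about 0.4 points at 0.9.
- Pain effect 0.9 NRS (half the planned effect): power for function 84.6% at correlation 0 and 82.4% at 0.7.
- No pain effect: gain 0.066 × 0.025 = 0.2 points, 81.3% to 81.5%.

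The gain is never negative.

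**Step 5: error control.** With both nulls true the familywise error is the same under either rule: 1 − 0.975² = 4.9% at correlation 0, and by simulation 4.6% at 0.5 and 4.3% at 0.7. With one null true, Holm tests that outcome at no more than 0.05, so the familywise error stays at or below 0.05.

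**The case against.** The strongest reply is that nothing here is wrong. The split is openly stated, suits two primary outcomes, controls familywise error and has figures that reproduce. Sizing function at 0.025 secures its 80% power whatever happens with pain, whereas Holm's extra power is conditional on the pain result. The split also gives 97.5% intervals that agree exactly with the tests, and the unseen analysis plan may already name Holm. All of this stands, and it makes the point optional. It does not remove the point, because Holm never rejects less, at the same error level.

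Three stronger readings are tempting and are not supported.

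- *Holm has more power for the stated and/or objective.* If that objective means at least one success, the two rules are identical (Step 3). The gain lies in claiming the second outcome.
- *The split wastes alpha or oversizes the trial.* Pain's 0.025 is spent on testing a primary outcome of equal standing. With both planned effects true, Holm would reach about 81% for function at 56 per arm, but that relies on the pain effect being real; under the split, 56 per arm gives 73%. This is no case for cutting N.
- *The Data Analysis section drops the split and leaves each outcome to a 5% test.* No section proposes 5% tests for each outcome; the only stated level is 0.025. Significance and interval levels can properly be left to the separate analysis plan.

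**Conclusion.** The fixed split is correct as written and can be improved. On the plan's own assumptions, Holm raises power for function from about 81% to 88% and power to claim both outcomes from 80-81% to 87-88%. The type II error for function falls from about 19% to 12%. Power for at least one outcome stays at 98.8-99.8%.

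The full gain rests on the planned pain effect of 1.8 NRS units being real. The assumed pain-function correlation hardly matters under the planned effects; it matters more when the pain effect is small. Two-sided testing is inferred from the reproduced sample size. This is an optional efficiency improvement.

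**What to change.** Before unblinding, put one sentence in the analysis plan, for example: *The two primary outcomes will be tested by the Holm procedure at a familywise two-sided alpha of 0.05: the smaller p-value against 0.025 and, if that is significant, the other against 0.05.* Keep N = 136 and describe the 0.025 calculation as conservative. If the analysis plan already says this, nothing is needed.

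The cost is one sentence, with no participants, data or conduct affected. The one drawback is in reporting: a second outcome claimed at 0.05 may have a 97.5% interval that includes zero. The plan should therefore say in advance which interval is reported for the primary outcomes, and that the claim rests on the Holm decision.
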